#### Sustainment

To examine whether perceptions of CQI and organizational readiness to change at the end of the intervention will predict CQI sustainment, we will explore bivariate relationships between innovation attributes (i.e., perceptions of the CQI’s relative advantage, complexity, observability, and trialability) and organizational climate as assessed at the end of the intervention with sustainment at end of Phase 2, examining the correlation between the two. We will have 80% power (alpha = 0.05) to detect whether PDSA Activity rating predicts at least 31% of the variance (e.g., R^2^ = 0.31) of each outcome; given the power limitations this should be regarded as a descriptive rather than inferential analysis.

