### Study design

The study is a group-randomized trial (GRT). Eight programs, stratified by modality (residential or outpatient), are being randomly assigned to receive the intervention either during the first study phase (these programs comprise ‘Cohort 1’) or the second (Cohort 2) (see Figure 1).

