##### *Sustainment*

To assess whether CQI activities are sustained, we plan to examine data collected from Cohort 1 during the Phase 1 implementation interviews and again during the Phase 2 period when the Cohort 1 programs are no longer receiving the intervention. These data will inform us about which CQI activities are sustained in Cohort 1 (if any), and about facilitators and barriers to sustainment. To collect these data, we are building upon the semi-annual implementation interview protocol in two ways. First, during the last set of Cohort 1 interviews, we are asking program staff about their plans to sustain CQI. Second, during the Cohort 2 intervention period, we are asking Cohort 1 staff whether the different components of the intervention are continuing, that is, whether regular CQI meetings are taking place.

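### The sustainment power statement (80% power at R² = 0.31) does not fit an outcome seen in, by inference, four programs, and it names a different predictor from the planned analysis

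*Protocol article*

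**What the plan says.** The Sustainment paragraph under Analytic methods plans to examine whether "perceptions of CQI and organizational readiness to change at the end of the intervention will predict CQI sustainment". It does so by relating innovation attributes and organizational climate "with sustainment at end of Phase 2, examining the correlation between the two". It then gives the power: "We will have 80% power (alpha = 0.05) to detect whether PDSA Activity rating predicts at least 31% of the variance". The article expresses this share as an R² of 0.31 and applies it to several outcomes. The same sentence ends with a caveat: "given the power limitations this should be regarded as a descriptive rather than inferential analysis".

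The Sustainment paragraph under Measures and procedures says where the outcome comes from: "we plan to examine data collected from Cohort 1 during the Phase 1 implementation interviews and again during the Phase 2 period". It also says what the outcome is: "we are asking Cohort 1 staff whether the different components of the intervention are continuing, that is, whether regular CQI meetings are taking place". The Study design section gives the number of units: "Eight programs, stratified by modality (residential or outpatient), are being randomly assigned to receive the intervention either during the first study phase". Study aims and hypotheses words the first sustainment hypothesis by program: programs with more CQI activity are expected to sustain more components.

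**The concern.** Two features of the power sentence do not match the analysis it sits beside.

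- **Unit.** Whether CQI meetings and other components continue has one value per program, apart from differences in how staff report it. A correlation with that outcome has as many independent points as there are Cohort 1 programs. An R² of 0.31 detectable with 80% power belongs to a sample several times larger.
- **Variables.** The planned correlation has perceptions and climate as predictors and sustainment as the single outcome. The power sentence has PDSA Activity as the predictor of each of several outcomes.

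A reader planning a later pilot could take 31% as the limit of what this design can detect about predictors of sustainment. The real limit for four programs is close to a perfect association.

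**Working it through.** **Inputs from the article**

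- Power 80%, alpha 0.05, R² = 0.31 (analytic section on sustainment; sidedness not stated there).
- Eight programs in two cohorts, stratified by modality, with four residential and four outpatient. Four programs in Cohort 1 is my inference; the split is not stated outright.
- Two staff per intervention program attend the CQI meetings, and the interviews are with staff involved in those meetings. That gives about 4 × 2 = 8 key staff in Cohort 1.
- Staff ICC 0.040 (Intervention efficacy).

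**Step 1: the sample size implied by the stated figure.** R² = 0.31 gives r = √0.31 = 0.557 and f² = 0.31/0.69 = 0.449.

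- Noncentral F, one fixed predictor, noncentrality n·f²: at n = 20, 20 × 0.449 = 8.99, with 1 and 18 df, and power is 0.809. At n = 19 it is 0.786. So n = 20.
- Fisher z, two-sided: n = 3 + [(1.960 + 0.842)/atanh(0.557)]² = 3 + (2.802/0.628)² = 22.9, so 23.
- Exact bivariate-normal correlation, two-sided: n = 22 (power 0.801).
- One-sided versions: n = 18 (exact) or 19 (Fisher z).

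The statement therefore reproduces at about 18 to 23 independent units, depending on method.

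**Step 2: where such a number could come from.** The Feasibility paragraph gives R² = 0.17 for PDSA Activity and staff-level outcomes. By noncentral F that needs n = 41, about twice 20. With ICC 0.040, 24 staff at six per program give 24/(1 + 5 × 0.040) = 24/1.20 = 20 effective units. So 0.31 is what the feasibility calculation would give for one cohort's staff. This is a plausible source, not a documented one.

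The ICC adjustment would not make the figure apply here. An ICC of 0.040 describes staff-reported measures, whereas sustainment has essentially one value per program.

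**Step 3: four programs.** With n = 4 there are 2 df and the critical t is 4.303. The critical |r| is 4.303/√(4.303² + 2) = 0.950, a sample R² of 0.90.

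| Units | Model | Power at R² = 0.31 |
|---|---|---|
| 4 | noncentral F, fixed predictor (noncentrality 4 × 0.449 = 1.80) | 0.130 |
| 4 | exact correlation, two-sided (simulation agrees) | 0.109 |
| 4 | exact correlation, one-sided | 0.19 |
| 8 | noncentral F, fixed predictor | 0.36 |
| 8 | exact correlation, two-sided | 0.31 |

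The eight-unit rows treat the key staff as independent, which is generous.

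The true R² needed for 80% power at n = 4 is 0.89 with a fixed predictor (noncentral F) and about 0.95 with a random predictor (simulated power 0.80 at R² = 0.95).

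**Step 4: the variables, side by side**

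| | Predictor | Outcome |
|---|---|---|
| Feasibility regression | PDSA Activity rating | each perception or readiness scale |
| Sustainment correlation | innovation attributes, organizational climate | sustainment at end of Phase 2 |
| Sustainment power sentence | PDSA Activity rating | each outcome |

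The third row has the variables of the first. This mismatch needs no assumption about sample size.

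**The case against.** The strongest reply is that the plan disclaims inference in the same sentence, and that its wording is exploratory throughout. The Feasibility paragraph says the significance of a coefficient will be examined; the sustainment paragraph announces no significance test. No sample size, design choice or conclusion depends on the 31% figure. This stands, and it is why the point is minor. It does not make the figure right: the caveat is attached to a power statement that does not belong to this analysis.

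The article also states no sample size here, so a count of about 20 is back-calculated, and four programs is inferred. Both must be worded as inferences. Every standard method nevertheless gives 18 to 23, far above any number of Cohort 1 programs possible with eight in the trial.

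An activity predictor is not foreign to the sustainment aim, since Study aims and hypotheses expects CQI activity to relate to sustainment. But the Feasibility paragraph treats the number of CQI activities and the PDSA Activity rating as different measures, and the planned sustainment correlations use neither.

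A reader might infer two stronger things. One is that the investigators counted about 20 programs, or plan an underpowered significance test of sustainment. The article gives no N and labels the analysis descriptive, so neither follows. The other is that the article recommends this power figure as a template for later pilots. The Discussion offers the study design as a template, not this figure.

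**Conclusion.** The point holds, with minor severity. The stated 80% power at R² = 0.31 requires roughly 18 to 23 independent units. For a program-level outcome in an inferred four programs, two-sided power is about 0.11 to 0.13, so an association of the stated size would be missed nearly nine times in ten. Separately, the sentence states power for a model that the sustainment paragraph does not plan.

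The numerical part assumes equal allocation of programs to cohorts and one sustainment value per program. The range reflects fixed versus random predictor; a one-sided test raises power at four programs only to 0.19. The predictor mismatch rests on the text alone.

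**What to change.** Delete the 80%/31% statement, or restate it for four programs and the predictors actually analysed. If restated, it should say that significance would need |r| of at least 0.95 and that 80% power would need a true R² of about 0.89 to 0.95.

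Keep the descriptive label. Report perceptions, readiness, CQI activity and components sustained program by program. Name the predictors consistently with Study aims and hypotheses, which lists CQI activity, perceptions and readiness. The current sustainment analysis omits CQI activity, and its list of perceptions leaves out compatibility.

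The cost is one or two sentences of text, with no change to data collection or design.

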#### Costs

Since the monthly cost surveys are activity-based and the interview questions on costs will provide details for how time on CQI activities were spent (e.g., additional work, part of work already doing), we will initially describe direct costs associated with key types of CQI activities. We will then aggregate these activities and use findings from the annual cost survey and interviews to provide a description of the direct and indirect costs of implementing CQI. Given the lack of information regarding CQI costs, we view this in itself as a contribution to the literature and to practitioners. Lastly, we will conduct a standard cost analysis comparing costs between the facilities that receive the intervention and facilities that had not yet, according to the cohort schedule.

## Discussion

The present study offers a much-needed, innovative strategy for implementing CQI in SUD treatment settings. While CQI may offer ways to improve SUD treatment, we cannot assume that it can be easily transported into practice or that it will have the same impact as it has had in more traditional healthcare settings [60]. Organizations do not always adopt new practices even when they are known to improve outcomes [61]. Further, attention needs to be paid to factors both at the individual and organizational levels that impact the degree to which new practices are adopted and implemented. For example, a number of studies have shown that factors at both the individual level (e.g., training, skills, efficacy, involvement in decision making, and job satisfaction) and at the organizational level (organization size, climate, and financial resources, and active leadership support) predict successful program implementation [61-66].

Our strategy for bringing CQI into SUD treatment settings addresses many of these needs and potential transportability barriers. First, collaboration with organizational leadership and their active participation in meetings and workshops helps tailor the intervention to the needs of the organization and lends credibility to the intervention. Next, the study provides clinical staff with skills to make small improvements to enhance treatment quality and involves them in decision-making and planning activities. And finally, through hands-on skill-building meetings and ongoing technical assistance, the intervention offers an active learning environment for staff at multiple levels.

Moreover, the study offers a unique design that provides a way to maximize the collection of feasibility, costs, efficacy, and sustainment of the intervention in a pilot study. In particular, data collection instruments were designed to permit a relatively comprehensive analysis of the intervention, yet were implemented so as to reduce the burdens of data collection and performance of multiple analyses. Although we are somewhat limited by testing the intervention in a single organization, it is recommended that early stage intervention studies take place in a single organization to eliminate the potential loss of power involved in statistically adjusting for organizational differences [67]. Another potential limitation of the study is that the proposed assessments (i.e., staff and client outcomes) may not adequately reflect change as the result of a type of CQI interventions selected. That is, because program staff determine the CQI improvement strategy and it is likely to differ across programs, it is not known how well a specific intervention will be aligned with the outcomes being evaluated in the study. To address this limitation, the study captures both staff and client level changes, as CQI strategy may influence one but not the other. This is also consistent with the results from CQI practiced in traditional health care settings, where studies have shown that CQI efforts have demonstrated tangible results to both patients and providers [68]. In summary, we hope that this study design offers a template for those wishing to efficiently study intervention feasibility, cost, efficacy, and sustainment in a pilot study which may shorten the time between intervention development and translation into real world practice settings.

## Abbreviations

ABC: Activity based costing; CQI: Continuous quality improvement; EBPAS: Evidence-based practice attitude scale; GRT: Group randomized trial; ICC: Intra-cluster correlation; IOM: Institute of Medicine; NIH: National Institutes of Health; ORC: Organizational Readiness for Change; PDSA: Plan-Do-Study-Act; SASCAP: Substance Abuse Services Cost Analysis Program; SD: Standard deviation; STM: Simpson transfer model; SUD: Substance use disorder; TCU SOF: Texas Christian University’s Survey of Organizational Functioning.
